# Comparison of hemostatic ability between spray coagulation and forced coagulation modes in endoscopic submucosal dissection in patients with early gastric neoplasms: a study protocol for multicenter randomized controlled trial (Spray-G trial)

**DOI:** 10.1186/s13063-023-07852-6

**Published:** 2024-01-15

**Keywords:** Endoscopic submucosal dissection, Gastric neoplasms, Spray coagulation mode, Hemostasis

## Abstract

**Background:**

Endoscopic submucosal dissection (ESD) is the standard treatment for early gastric neoplasms (EGN). Controlling intraoperative bleeding is crucial for ensuring safe and reliable procedures. ESD using the spray coagulation mode (SCM-ESD) has been developed to control bleeding more effectively than ESD using the conventional forced coagulation mode (FCM-ESD). This study aims to compare the hemostatic efficacies of SCM-ESD and FCM-ESD.

**Methods:**

This multicenter, prospective, parallel, randomized, open-label superiority trial will be conducted in five Japanese institutions. Patients with a preoperative diagnosis of intramucosal EGC will be randomized to undergo either SCM-ESD or FCM-ESD. The primary outcome measure is the completion of ESD with an electrosurgical knife alone, without the use of hemostatic forceps. Secondary outcomes include the number and duration of hemostasis using hemostatic forceps, procedure time, curability, and safety. A total of 130 patients will be enrolled in this study.

**Discussion:**

This trial will provide evidence on the hemostatic efficacy of SCM-ESD compared with FCM-ESD in patients with intramucosal EGN, potentially improving the safety and reliability of ESD procedures.

**Trial registration:**

The trial has been registered at the University Hospital Medical Information Network Clinical Trials Registration (UMIN-CTR) as UMIN000040518. The reception number is R000054009.

**Supplementary Information:**

The online version contains supplementary material available at 10.1186/s13063-023-07852-6.

## Introduction

### Background and rationale {6a}

Endoscopic resection (ER) is the standard treatment for early gastric neoplasms (EGN) with a negligible risk of lymph node metastasis [1]. ER is a minimally invasive treatment that preserves organ function, leading to a better post-procedure quality of life than surgery [2]. Endoscopic mucosal resection (EMR), the first form of ER, was developed to treat EGN. However, snaring techniques have limitations, particularly in terms of the piecemeal resection of large or ulcerated lesions, leading to difficulties in accurate histological assessment and a high risk of local recurrence. Endoscopic submucosal dissection (ESD) using an electrosurgical knife has been developed to overcome these limitations. ESD allows en bloc resection of large or ulcerated lesions, resulting in accurate histological assessment and a reduced risk of local recurrence [3, 4]. Despite its higher curative potential, ESD is reported to be more difficult to perform, with a longer procedure time and higher adverse event rates, including bleeding and perforation, than EMR [3, 4]. Controlling intraoperative bleeding during ESD is crucial for a safe and reliable procedure [5]. In cases of intraoperative bleeding or exposed vessels, the coagulation wave of the electrosurgical knife is used to cauterize the area. In more severe cases, hemostatic forceps may be employed if it is difficult to control bleeding or vessels with a knife alone [6].

In ESD, two basic electrocautery patterns of an electrosurgical unit are employed: cut current and coagulation current [7]. Cut current is mainly used for mucosal incisions, whereas coagulation current is used for submucosal dissection and hemostasis. Forced coagulation mode (FCM) is conventionally used as the coagulation current [8, 9]. VIO3 (ERBE, Germany) is the latest high frequency unit (HFU), which has been developed to improve the performance of the electrosurgical knife in ESD. VIO3 facilitates submucosal dissection via coagulation currents. The spray coagulation mode (SCM), with a higher peak voltage and shorter duty cycle, possessed greater coagulation ability than conventional FCM [10–13]. Recently, ESD with SCM in VIO3 (SCM-ESD) has been developed to control procedure-related bleeding more effectively than FCM (FCM-ESD). Our pilot data showed that SCM-ESD reduced the use of hemostatic forceps as a rescue device by 28% while maintaining high curability and safety. To confirm the hemostatic efficacy of SCM-ESD, we aim to conduct a multicenter randomized controlled trial to compare the clinical outcomes of SCM-ESD and FCM-ESD.

### Objectives {7}

This study aims to investigate the hemostatic efficacy of SCM-ESD and FCM-ESD in patients with EGN.

### Trial design {8}

This is a prospective, parallel, randomized, open-label superiority trial. The trial design adheres to the recommendations of the Standard Protocol Items: Recommendations for Interventional Trials (SPIRIT) checklist (Additional file 2) [ [14]. Patients with a preoperative diagnosis of EGN are enrolled and randomly assigned to one of two interventional arms: SCM-ESD or FCM-ESD. A flowchart of the trial design is illustrated in Fig. 1.

**Fig. 1 Fig1:**
[figure not shown]
Schematic of the study design. SCM-ESD, spray coagulation mode endoscopic submucosal dissection; FCM-ESD, forced coagulation mode endoscopic submucosal dissection; ESD, endoscopic submucosal dissection

## Methods: participants, interventions and outcomes

### Study setting {9}

This multicenter trial will be conducted across five institutions in Japan: Kitakyushu Municipal Medical Center, Kyushu University Hospital, Saiseikai Futsukaichi Hospital, Fukuoka Central Hospital, and the National Hospital Organization Ureshino Medical Center.

### Eligibility criteria {10}

The eligibility criteria for this study include the following: (i) patients with lesions endoscopically diagnosed as EGN and eligible for ESD, (ii) patients with lesions diagnosed by endoscopic biopsy as gastric adenomas or adenocarcinomas, (iii) patients with age ≥ 20 years at the time of consent, (iv) patients with Eastern Cooperative Oncology Group Performance Status of 0–2, and (vi) patients capable of understanding the study explanations and providing signed consent. Exclusion criteria for this study include the following: (i) patients with a history of gastric surgery, (ii) patients currently undergoing dialysis, (iii) patients requiring perioperative heparin administration, (iv) patients with contraindications to endoscopy, and (v) patients deemed inappropriate by the investigators for the study.

### Who will take informed consent? {26a}

The investigator will thoroughly explain the details of the trial to the potential patients, including the benefits and risks associated with the two treatment procedures. If patients express a willingness to participate, written informed consent for the trial will be obtained from the patients.

### Additional consent provisions for collection and use of participant data and biological specimens {26b}

If the patients agree to participate, additional written informed consent will be obtained to collect biological samples for histopathological assessment. The potential for secondary use of the samples and information obtained from this trial will be explained to the participants. These samples will be stored in a freezer in a locked laboratory for at least 5 years after the completion of the trial and then properly disposed of in accordance with the Kyushu University Standard Operating Procedures for the Storage of Samples and Information Obtained from Human Subjects.

## Interventions

### Explanation for the choice of comparators {6b}

The enrolled patients will be randomized to receive either SCM-ESD or FCM-ESD. FCM-ESD was selected as the control comparator because FCM is conventionally used as the coagulation current during ESD.

### Intervention description {11a}

As for operators, this trial will be conducted at institutions where ESD for EGN is performed regularly. Experienced endoscopists specialized in endoscopic diagnosis and treatment will exclusively perform ESD procedures in this trial. The criteria for skilled endoscopists are as follows: (i) completion of the postgraduate clinical training system in Japan for more than 2 years and involvement in endoscopic diagnosis and treatment, (ii) experience with at least1000 cases of endoscopy, and (iii) experience with more than 30 cases of ESD. In principle, a single operator will be responsible for completing the ESD procedure. However, a temporary or permanent operator change to a more skilled supervisor will be allowed in the following cases, prioritizing patient safety: (i) prolonged procedure time of ≥ 60 min for ESD, (ii) one instance of hemostasis requiring ≥ 10 min, (iii) occurrence of intraoperative perforation, or (iv) cases in which the supervisor deems the operator change necessary. Any temporary or permanent changes in the operators will be recorded.

As for equipment and setting, ESD will be performed using upper gastrointestinal therapeutic endoscopes (GIF-Q260J and GIF-H290T; Olympus, Tokyo, Japan) equipped with disposable hoods (not regulated). An injection needle (not regulated) will be used for submucosal injection with hyaluronic sodium or alginate sodium as the injection solution. ProKnife (Boston Scientific, Tokyo, Japan) will be utilized for various aspects of both SCM-ESD and FCM-ESD procedures including marking, mucosal incision, submucosal dissection, and hemostasis [15, 16]. HemoStat-Y (Pentax, Tokyo, Japan) will be used as the hemostatic forceps. The HFU used in this trial will be VIO3. The following settings will be employed for the electrosurgical knife on the HFU: during incision, end-cut I mode with effect 1 (ranging 1–3), duration 2 (ranging 1–3), and interval 1 (ranging 1–3); during submucosal dissection and hemostasis in FCM-ESD, forced coagulation mode with effect 5 (ranging 4–6); during submucosal dissection and hemostasis in SCM-ESD, spray coagulation mode with effect 5 (ranging 4–7). The setting of the HFU for the hemostatic forceps will be the bipolar-soft coagulation mode with Effect 5 (ranging 4–6) with the quick-start mode activated.

As for ESD procedure, in principle, ESD will be performed for en bloc resection of a target lesion using an electrosurgical knife. However, if en bloc resection is not feasible owing to certain circumstances, alternative strategies such as piecemeal resection or additional ablation techniques such as argon plasma coagulation or hot biopsy may be employed to prevent residual tissue. After identifying the lesion, circumferential marking dots will be made placed approximately 2–3 mm outside the lesion using the tip of the knife. An injection needle will then be introduced from outside the markings, and a viscous solution will be injected into the submucosal layer beneath the lesion. After confirming elevation of the lesion, an initial mucosal incision will be made outside the marking using a knife. After completing the circumferential mucosal incision, submucosal dissection will be initiated using a knife. Traction assistance can be provided in the direction of the operator. Additional local injections can be administered using either the injection needle or the tip of the knife as the mucosal incision or submucosal dissection progresses. The volume of solution injected from the injection needle will be recorded. Dissection will continue until the lesion is excised with a knife. In cases of bleeding during mucosal incision or submucosal dissection, initial hemostasis will be attempted by coagulation with the tip of a knife. However, if bleeding cannot be controlled using a knife alone, hemostatic forceps will be employed as a rescue device. Forceps will be used to grasp the bleeding vessels, followed by coagulation. The criteria for transitioning to hemostatic forceps are as follows: (i) complete hemostasis cannot be achieved within 30 s using the knife; (ii) if the operator determines that bleeding is difficult to control with the knife alone; or (iii) if the operator determines that dealing with the exposed vessel using the knife alone is challenging. Transitioning to hemostatic forceps will be permitted if (ii) or (iii) is met, even if (i) is not fulfilled, to ensure patient safety. If hemostatic forceps are employed, hemostasis with the forceps will continue until the bleeding is completely stopped. The number and duration of hemostatic forceps used will be also recorded. The use of other devices that are not regulated may be allowed based on the operator’s judgment and such instances will be recorded.

As for pathological assessment, the specimens will be fixed on a plastic plate and sliced at 2-mm intervals. Pathological diagnoses will be made by pathologists at each participating institution following the Japanese Classification of Gastric Carcinoma [17].

### Criteria for discontinuing or modifying allocated interventions {11b}

If hemostasis with hemostatic forceps is required more than five times during SCM-ESD or FCM-ESD, transitioning from SCM-ESD to FCM-ESD or from FCM-ESD to SCM-ESD will be allowed for safety reasons. Such a conversion will not constitute a protocol deviation that will be duly recorded.

### Strategies to improve adherence to interventions {11c}

No specific strategies have been established to improve patient adherence to interventions because the focus of this trial is primarily on the ESD procedure.

### Relevant concomitant care permitted or prohibited during the trial {11d}

To prevent delayed bleeding, proton pump inhibitors or potassium-competitive acid blockers can be administered daily, starting from the date of ESD and continuing until discharge.

The concomitant use of antithrombotic agents, excluding continuous heparin, will be permitted throughout the study period, following the Japanese guidelines for gastroenterological endoscopy in patients undergoing antithrombotic treatment [18].

After treatment, patients will be kept on a fasting regimen and administered an intravenous drip. Oral intake will be resumed 2–3 days after ESD, starting with a liquid or soft diet, and gradually transitioning to a normal diet.

### Provisions for post-trial care {30}

Proton pump inhibitors or potassium-competitive acid blockers can be administered to patients for up to eight weeks from the date of ESD to prevent delayed bleeding.

No special compensation will be provided, because it is not anticipated that any harm will result from participating in this study.

### Outcomes {12}

The primary outcome is successful completion of ESD using an electrosurgical knife alone, which is considered an important indicator reflecting the hemostatic ability to control intraoperative bleeding. If hemostatic forceps are required as a rescue device to achieve hemostasis prior to tumor retrieval, the procedure will be considered a failure. Secondary outcome includes the number and duration of hemostasis performed with hemostatic forceps; procedure time, including total ESD time, mucosal incision time, and submucosal dissection time; speed of submucosal dissection; en bloc resection rate; complete resection rate; curative resection, evaluated based on endoscopic curability (A or B); degree of each endoscopic curability category; thickness of the submucosal layer in the resected specimen; type and volume of submucosal injective solution used; occurrence of operator change; and adverse events. Total ESD time is divided into mucosal incision time and submucosal dissection time. The continuous outcome data will be analyzed without any categorization.

Outcome without histopathological assessments will be evaluated at ESD. Outcomes with histopathological assessments including complete resection rate; curative resection, evaluated based on endoscopic curability (A or B); degree of each endoscopic curability category; and thickness of the submucosal layer in the resected specimen will be evaluated within 1 week after ESD.

### Participant timeline {13}

The participants’ timelines are shown in Fig. 2. The protocol adheres to the Standard Protocol Items: Recommendations for Interventional Trials (SPIRIT) guidelines.

**Fig. 2 Fig2:**
[figure not shown]
SPIRIT flow diagram. SCM-ESD, spray coagulation mode endoscopic submucosal dissection; FCM-ESD, forced coagulation mode endoscopic submucosal dissection

### Sample size {14}

In our previous pilot study comparing the outcomes of SCM-ESD and FCM-ESD for the same subjects as in this study, the completion rate of ESD with the electrosurgical knife alone in SCM-ESD was 62.5% (40/64) compared to 34.6% (9/26) in FCM-ESD, resulting in a difference of 27.9%. Considering the variability in ESD outcomes among institutions, we assumed a 25% additive effect of SCM-ESD over FCM-ESD on the completion rate. The required number of cases was determined using the *χ*^2^ test with a two-sided alpha significance level of 5% and a power of 80%, resulting in a total required number of 62 case per group (124 cases in total). Considering a dropout rate of approximately 5% for ineligible patients, we calculated that 65 patients per group (130 patients in total) would be required.

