## Assignment of intervention: allocation

### Sequence generation {16a}

Upon obtaining patient consent, the investigator will register the patient in the database of the UMIN Medical Research Support Cloud version, UMIN INDICE Cloud, which serves as a web-based central randomization system. Each patient will be assigned a unique identification number for registration. The registration process will only be accepted if all the required data are provided. After confirming the eligibility on the registration screen, a registration number will be generated. The UMIN INDICE cloud will facilitate both immediate and concealed allocations. Registered patients will be randomized (1:1) into either the SCM-ESD or FCM-ESD groups using dynamic balancing, employing a minimization method based on tumor location (upper or middle third of the stomach vs. lower third of the stomach), tumor size (0–20 mm vs. > 20 mm), and the use of thrombotic agents (presence vs. absence).

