## Statistical methods

### Statistical methods for primary and secondary outcomes {20a}

With regard to the primary outcome as the completion of ESD with the knife alone, the two groups will be compared using the Cochran-Mantel–Haenszel test stratified by lesion location (upper or middle third of the stomach vs. lower third of the stomach), lesion size (0–20 mm vs. 21 mm or more), and presence of antithrombotic agents (continued, discontinued, or not administered). If SCM-ESD significantly outperforms FCM-ESD (two-sided significance level of 5%), we will conclude that SCM-ESD is a more useful treatment method than FCM-ESD.

With regard to secondary outcomes, the number and duration of hemostasis using hemostatic forceps and procedure time will be analyzed using the Wilcoxon rank-sum test. The speed of dissection, thickness of the submucosal layer in the resected specimen, and volume of the submucosal injection solution will be analyzed using *t*-tests. En bloc resection, complete resection, curative resection, severe thermal damage to the resected specimen, type of submucosal injection solution, operator change, and occurrence of adverse events will be analyzed using Fisher’s exact test.

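### Sample size section cites outcome variation among institutions, but neither allocation nor any listed analysis uses institution: a precision and reporting gap, not a bias

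*Protocol article*

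**What the plan says.** The article's Sample size section reports pilot completion rates of 62.5% (40/64) with spray coagulation and 34.6% (9/26) with forced coagulation, a difference of 27.9 points. It then plans on a smaller difference: "Considering the variability in ESD outcomes among institutions, we assumed a 25% additive effect". That leads to 62 per group before dropout. Study setting names five institutions.

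Three other sections list the factors that the design and analysis use:

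- Sequence generation allocates by "employing a minimization method based on tumor location", with tumour size and use of thrombotic agents (present or absent) as the other two factors.
- Statistical methods fixes the primary test: "the two groups will be compared using the Cochran-Mantel–Haenszel test stratified by lesion location", lesion size and antithrombotic status, the last in three levels. The secondary outcomes get unadjusted Wilcoxon, t and Fisher tests.
- Methods for additional analyses gives the subgroups as location, size, antithrombotic use, ESD experience and pathological ulceration.

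Institution is in none of these lists. Trial status adds that recruitment closed on February 21, 2023.

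**The concern.** The plan treats institution as a real source of variation when it sizes the trial, then makes no use of it. Shrinking the assumed effect enlarges the trial, but it neither balances institutions between arms nor removes their differences from the comparison.

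Institution could plausibly matter here. The primary outcome fails when hemostatic forceps are used as rescue. Under the Intervention description, two of the three grounds for moving to forceps are the operator's judgement, so local habit can shift the completion rate.

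At stake is precision, and the ability to show readers whether the result rests on one or two institutions. Institution is a baseline factor known for every patient, so using it needs no new data.

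**Working it through.** **1. The plan's own sample size.** Inputs from the Sample size section: two-sided 5%, 80% power, control 34.6%, difference 25 points (so 59.6%).

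n = [1.960·√(2·p̄·(1−p̄)) + 0.842·√(p1(1−p1) + p2(1−p2))]² / (p2−p1)²

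- 34.6% vs 59.6%: p̄ = 0.471, giving (1.384 + 0.575)² / 0.0625 = 61.4, so 62 per group. The stated figure reproduces.
- 34.6% vs 62.5% (pilot): p̄ = 0.4855, giving (1.385 + 0.571)² / 0.0778 = 49.2, so 50 per group.

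The allowance attributed to institutions is therefore 62 − 50 = 12 patients per group.

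**2. Chance imbalance from institution mix.** The between-institution spread is an assumption: SD 0, 0.5 or 1.0 on the log-odds scale. Control rates by institution then run from about 20% to 51% at SD 0.5 and about 10% to 66% at SD 1.0. With N = 124 allocated 1:1 and institution ignored, the SD of the between-arm difference due to mix alone is roughly s·√(4/N), where s is the SD of the institution rates.

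- SD 0.5, equal-sized institutions (26, 51, 34, 20, 42%): s = 11.1 points; 11.1 × 0.180 = 2.0 points.
- SD 1.0 (18, 65, 31, 10, 48%): s = 20.0 points; 20.0 × 0.180 = 3.6 points.

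Simulation (4,000 trials per setting, equal and unequal institution sizes) gave 1.9–2.0 and 3.6–3.7 points, against about 0.3 and 0.5 had institution been balanced.

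For scale, the standard error of the whole difference is √[(0.346·0.654 + 0.596·0.404)/62] = 8.7 points. Institution mix is part of that error, not an addition to it: about (2.0/8.7)² = 5% of the variance at SD 0.5 and (3.6/8.7)² = 17% at SD 1.0.

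**3. Power, like for like.** Simulated trials of 124 patients in five institutions, 34.6% vs 59.6%:

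| Assumed SD | Planned CMH, 12 strata | Score test, three factors | Score test, three factors + institution |
|---|---|---|---|
| 0 | 77% | 81% | 80% |
| 0.5 | 78% | 82% | 83% |
| 1.0 | 79% | 83% | 87% |

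A repeat (2,500 trials per setting, institution sizes 35/25/15/15/10%, no covariate effects) gave 78/78/80, 82/82/82 and 81/82/87%. The simulation error of one such figure is √(0.8·0.2/2500) = 0.8 points.

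- Institution itself (column 4 minus column 3): about −1, 0 to +1, and +4 to +5 points.
- Leaving the 12-stratum CMH for a main-effects model (column 3 minus column 2): +4, +4, +4 in the table and +4, +4, +2 in the repeat, so about 3 to 4 points. This has nothing to do with institution.

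**4. Type I error.** Tests that ignore institution stayed near 5% (4.6–5.6%). For the model with institution, the likelihood-ratio test ran at 6–7% and the score test at 5.6–6.9%. Some of the model's apparent gain over the CMH is therefore bought with a slightly raised error rate.

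**5. Crossing institution with the planned strata.** 2 × 2 × 3 = 12 strata; 12 × 5 = 60 cells; 124/60 ≈ 2 patients per cell.

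**The case against.** The strongest reply is that the planned test is valid without institution, and that lowering a pilot effect when moving to five institutions is ordinary caution that commits nobody to adjust. Both points stand. A reader might infer bias, an inflated error rate, a wrong sample size or a self-contradiction. None follows: allocation is by individual patient, simulated type I error is near 5%, and 62 per group reproduces.

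The benefit also depends on a spread that no document gives. All institutions share one knife, one generator, one model of forceps and a floor of operator experience ("experience with more than 30 cases of ESD"), so SD 1.0 may be extreme, and at SD 0.5 the power gain is about nil. That stands too, and limits the size of the point.

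A reader might set 77–79% for the CMH against 80–87% for the full model and credit institution with the whole gap. The like-for-like column shows that most of it, except at SD 1.0, comes from the change of test.

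A reader might also infer that operators could be picked knowing the arm, since the trial is open-label. The article does not say when the operator is chosen, or that a planned operator is recorded before allocation, so it supports neither that argument nor an adjustment built on it.

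Finally, consistency across institutions may be dealt with in an analysis plan not shown, so it cannot be called unexamined. What remains is that the article fixes the primary test and lists the factors explicitly, and institution is absent although the article itself cites it.

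**Conclusion.** The point holds as a matter of precision and reporting. The plan relies on institutional variation to set its effect size and then leaves it uncorrected in the primary comparison. The consequence is a chance shift of about 2 to 4 points (1 SD) at assumed logit SDs of 0.5 to 1.0. The power forgone is about 0 points up to SD 0.5 and about 4 to 5 at SD 1.0. A further 3 to 4 points would come from replacing the 12-stratum CMH with a main-effects model, before correcting that model's slightly raised type I error.

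All of this rests on assumed spreads and institution sizes. It is worth fixing because the remedy is cheap, not because the planned test is unsound.

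**What to change.** Before results are examined, pre-specify a logistic model with arm, the three minimisation factors in the categories used at allocation, and institution, all as main effects. Report a standardised risk difference with 95% CI. Take the p-value from re-randomisation, repeating the minimisation as it was actually run, because likelihood-ratio and score tests sit slightly above 5% here.

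Use this as the primary analysis or, at minimum, as a named adjusted analysis beside the CMH test. Show effects by institution descriptively only: an institution with 10% of patients would have about 12, or 6 per arm.

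Do not cross institution with the CMH strata (60 cells). A CMH test stratified by institution alone is workable but costs about 3 power points against the unstratified test if institutions do not differ (81.8% to 78.5% and 82.0% to 79.4% in the simulations). Minimisation cannot change, since recruitment has closed.

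Cost: one more model, 4 degrees of freedom, no new patients or data, and up to about 1 power point if institutions do not differ.
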